### Outcomes

2.9

The primary efficacy evaluation will focus on the assessment of average pain intensity in NCNP patients over the past week at 8, 20, and 30 weeks after randomization. Secondary outcomes will include quality of life, emotional distress, sleep quality, and work efficiency.

At each assessment point, data will be collected by independent clinical research coordinators who are blinded to group allocation.

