**Methods and analysis:**

A total of 110 NCNP patients aged 18 to 50 years will be recruited. Participants will be randomly assigned in a 1:1 ratio to either the TCB group or Baduanjin group. Each group will undergo a total of 16 sessions of therapy over 8 weeks, with two sessions per week. Outcomes will be assessed at week 8, 20, and 32 post-randomization. The primary outcome is the pain intensity at week 8, assessed by the visual analogue scale scores (VAS). Secondary outcomes include functional disability (evaluated with the Neck Disability Index), quality of life (assessed using the 12-item Short Form Survey questionnaire), emotional distress (measured by the Hospital Anxiety and Depression Scale), sleep quality (evaluated with the Pittsburgh Sleep Quality Index), work efficiency (assessed using the Work Productivity and Activity Impairment Questionnaire-Specific Health Problem), and safety. The statistical analyses will follow the two-way repeated measures analysis of variance to compare clinical data between groups across different time points.

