### Study design

2.1

This study is a randomized, assessor-blinded, single-center, two-arm, parallel-group superiority trial. The protocol was approved by the Ethics Committee of Yueyang Hospital of Integrated Traditional Chinese and Western Medicine, Shanghai University of Traditional Chinese Medicine (project number: 2023-143), and registered at the Chinese Clinical Trial Registry (ChiCTR2300073680). This study will follow the strict criteria outlined in the Consolidated Standards of Reporting Trials (CONSORT) and the Standard Protocol Items: Recommendations for Interventional Trials (SPIRIT) guidelines.

A total of 110 participants will be recruited from the Tuina Department of Shanghai Yueyang Hospital and randomly assigned (1:1) to either the Baduanjin group or the TCB group. The trial includes an 8-week intervention period and a 24-week follow-up. Baseline characteristics will be collected prior to randomization, and outcomes (pain, functional impairment, quality of life, adverse events) will be assessed at weeks 8, 20, and 32. The study procedures are illustrated in a flowchart (Figure 1), with the intervention and outcome schedule detailed in Table 1.

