#### Primary outcome

2.9.1

The primary outcome is the self-reported average pain intensity over the past week at week 8 post-randomization, assessed using the VAS. VAS is a 10-cm horizontal scale anchored by [0] on the left end, indicating “no pain”, and [10] on the right end, indicating the “worst pain”. Higher scores reflect greater pain intensity relative to baseline (27). The VAS was demonstrated to be a valid, responsible, concise and easily interpreted outcome measure with intraclass correlation = 0.92 (28).

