### Statistical analysis

2.11

All statistics were performed by independent statisticians using SPSS software (version 24.0, SPSS Inc., Chicago, IL, USA). The primary and secondary outcomes will be analyzed based on the intention-to-treat principle. Primary outcome analysis will be adjusted for baseline VAS and other prespecified covariates using ANCOVA or multiple linear regression if baseline imbalance is observed. Based on MCID of 1.5 points, the proportion of participants achieving MCID will be calculated. Occupation (sedentary vs. non-sedentary work) will be included as a stratification variable in WPAI-SHP analysis. All between-group comparisons will base on the change score of a specific time point and the baseline. Baseline characteristics will be summarized in a table and compared between groups to assess comparability. Missing values for dropout cases will be imputed using either the last observation carried forward method if the dropout rate is below 5% or the multiple imputation method for a dropout rate of 5% or higher. Descriptive statistics will be presented as mean ± SD for continuous variables that follow a normal distribution and as median (IQR) for those that do not follow a normal distribution, based on the results of normality tests. For ordinal variables, the data will be presented as median (IQR) or frequency (*n*, %) depending on the nature of the data. Categorical variables will be summarised as *n* (%). To analyse trends over time and the interaction between groups and times, two-way repeated measures analysis of variance will be used to compare clinical data at multiple observation time points.

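### Section 2.9 puts primary pain at weeks 8, 20 and an unscheduled week 30 against week 8 elsewhere, and no single unconditional week-8 test is named

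*Protocol article*

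**What the plan says.** On the time point, the protocol article says two things.

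- Section 2.9 (Outcomes) describes the primary efficacy evaluation as "average pain intensity in NCNP patients over the past week at 8, 20, and 30 weeks after randomization". The secondary outcomes it then lists are other domains, so pain at the later visits is not placed among them.
- Section 2.9.1 (Primary outcome) follows at once with one visit: "The primary outcome is the self-reported average pain intensity over the past week at week 8 post-randomization, assessed using the VAS". The abstract agrees: "The primary outcome is the pain intensity at week 8, assessed by the visual analogue scale scores (VAS". Section 2.7 also sizes the trial on the week-8 difference.

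On the schedule, the abstract, section 2.1, Table 1 and section 2.8 all give weeks 8, 20 and 32; section 2.1, for example, says that outcomes "will be assessed at weeks 8, 20, and 32". No week-30 visit exists.

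On the analysis, the abstract names one method: "The statistical analyses will follow the two-way repeated measures analysis of variance to compare clinical data between groups across different time points". Section 2.11 contains three separate statements:

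- the primary outcome is adjusted for baseline VAS and other covariates by ANCOVA or multiple linear regression, on condition that baseline imbalance is observed;
- all between-group comparisons use the change from baseline at a given visit;
- for trends and the group-by-time interaction, "two-way repeated measures analysis of variance will be used to compare clinical data at multiple observation time points".

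**The concern.** A superiority trial needs one primary quantity and one test of it, fixed before outcome data are seen. Here the section that defines the outcomes disagrees with itself about whether primary pain is measured at one visit or three, and one of the three does not exist. The analysis text does not settle the matter: the method in the abstract answers a different question from the week-8 difference on which the trial was sized, and the method section 2.11 attaches to the primary outcome depends on what the baseline data look like.

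At stake is the choice of result. Whichever test is finally called primary, some published sentence would support it and another would contradict it. That leaves room for choice after the results are known.

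**Working it through.** **1. Time point, statement by statement.**

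| Place | Primary pain assessed at |
|---|---|
| Abstract | week 8 |
| Section 2.7 | week 8 |
| Section 2.9 | weeks 8, 20, 30 |
| Section 2.9.1 | week 8 |

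Three places agree and section 2.9 is the outlier. Replacing 30 by 32 removes the impossible visit but still leaves three primary time points in section 2.9.

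**2. What the repeated-measures ANOVA tests.** Let d0, d8, d20 and d32 be the between-group differences in mean VAS at baseline and the three later visits (the VAS rows of Table 1).

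- The group effect tests (d0 + d8 + d20 + d32)/4 = 0. Week 8 carries a quarter of the weight.
- The group-by-time test asks whether d0 = d8 = d20 = d32. It rejects when the profiles differ anywhere.

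Neither is a test of d8 = 0, and neither gives an estimate of d8. If the ANOVA is run on the three change scores instead, a constant benefit produces no interaction at all.

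**3. Type I error if any of three visits counted.** This success rule is assumed; the document does not state it.

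- Independent visits: 1 − 0.95³ = 0.143.
- Correlated test statistics, by simulation: 0.135, 0.125 and 0.109 for assumed between-visit correlations of 0.3, 0.5 and 0.7.

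**4. Behaviour of the tests.** Inputs: 55 per group with 80% follow-up (section 2.7) gives 55 × 0.80 = 44 evaluable per group. Assumed: equal SD at every visit and equal correlation between visits, 0.5 unless stated. At correlation 0.5 the SD of a change score equals the visit SD, since √[2(1 − 0.5)] = 1, so the protocol's 1.1 can stand for either.

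No effect at week 8, benefit only at weeks 20 and 32:

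| Late effect, SD | Week-8 ANCOVA | Interaction (4 visits) | Group effect (4 visits) |
|---|---|---|---|
| 0.8, 1.5 (assumed) | 5% | 85% | 34–36% |
| 0.7, 1.1 | 5% | 96% | 48% |
| 1.5, 1.1 (planning values) | 5% | 100% | 98% |

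Effect at week 8 that falls to a half at week 20 and a quarter at week 32:

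| Week-8 effect, SD | Week-8 ANCOVA | Interaction (4 visits) | Group effect (4 visits) |
|---|---|---|---|
| 0.8, 1.5 (assumed) | 80–81% | 56–58% | 27–29% |
| 1.5, 1.1 (planning values; correlation 0.3–0.7) | about 100% | at least 99.9% | 87–98% |

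Hand check of the last group-effect figure at correlation 0.5: mean effect (0 + 1.5 + 0.75 + 0.375)/4 = 0.656. The SD of a participant's four-visit mean is 1.1 × √[(1 + 3 × 0.5)/4] = 0.870. The standard error is 0.870 × √(2/44) = 0.185. The ratio is 3.54, and power is about Φ(3.54 − 1.96) = 94%, inside the simulated range.

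With a constant effect of 1.5 and SD 1.1, the interaction on the three change scores rejects in about 5% of trials, while the group effect on the same scores rejects in practically all.

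**5. Choosing among tests.** With no effect at any visit (SD 1.1, correlation 0.5), taking the best of the week-8 change-score test, the group effect and the interaction rejects in about 12% of trials. This too needs a choice that the document does not announce.

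**The case against.** The strongest reply is that week 8 is plainly intended. It stands in the formal definition under the heading Primary outcome, in the sample size section and in the abstract; section 2.9 is a lead-in paragraph, the 30 looks like a slip for 32, and the Discussion treats week 32 as a maintenance assessment. This stands as a matter of intent. It does not reconcile the text, because section 2.9 lists three visits even once 30 is corrected.

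Second, a reader might infer from the abstract that the repeated-measures ANOVA is the primary test. The documents do not go that far. The abstract applies it to clinical data in general, and section 2.11 confines it to trends and interaction, offers visit-specific change-score comparisons and names ANCOVA or regression for the primary outcome. What remains is that the adjusted analysis is conditional on observed imbalance and no test is named for when none is seen. A fuller plan may supply the detail, but any choice it makes has to depart from one of these statements.

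Third, a reader might infer that error is in fact inflated to 11–13.5%, or that the trial is likely to miss a real week-8 effect. Neither is supported. No sentence makes success at any one visit sufficient. The large power losses need an effect of 0.8 and SD of 1.5, which are not the protocol's values; with 1.5 and 1.1 the same fade costs almost nothing. Benefit that appears only after treatment ends is a stress case, since section 2.8 provides no study treatment after week 8.

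**Conclusion.** The point holds as an inconsistency in the primary time point together with an unfixed primary test. Section 2.9 contradicts the abstract, section 2.7 and section 2.9.1 on the number of primary visits, and contradicts the schedule on the last one. No single unconditional test of the week-8 difference is fixed: the abstract's method does not estimate it, and the ANCOVA or regression in section 2.11 depends on the baseline data.

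The size is conditional. Type I error of about 11% to 13.5% applies only under an any-of-three rule with assumed correlations of 0.7 to 0.3. The mismatch between test and question does not depend on those assumptions: an interaction can be significant with no week-8 effect. Loss of power is small under the planning values for an effect that fades, apart from the interaction on change scores, which cannot detect a constant benefit at any effect size. The failing lies in what would be tested and claimed, more than in the chance of detecting the planned difference.

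**What to change.** - **Section 2.9:** state VAS pain at week 8 as the sole primary outcome, and list VAS at weeks 20 and 32 (not 30) as secondary.
- **Abstract and section 2.11:** name one primary test, applied whatever the baseline comparison shows: the between-group difference at week 8 from ANCOVA adjusted for baseline VAS, with its 95% confidence interval. Section 2.11 already names ANCOVA, so this removes a condition and adds no new method.
- **Repeated-measures analysis:** label it supportive or secondary, for the course over weeks 8, 20 and 32.

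The cost is wording in the protocol and analysis plan. Visits, sample size and data collection are untouched. The change should be dated before outcome data are seen by group, because afterwards it could be taken for a choice made on the results.

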#### Primary outcome

2.9.1

The primary outcome is the self-reported average pain intensity over the past week at week 8 post-randomization, assessed using the VAS. VAS is a 10-cm horizontal scale anchored by [0] on the left end, indicating “no pain”, and [10] on the right end, indicating the “worst pain”. Higher scores reflect greater pain intensity relative to baseline (27). The VAS was demonstrated to be a valid, responsible, concise and easily interpreted outcome measure with intraclass correlation = 0.92 (28).

#### Secondary outcomes

2.9.2

##### Neck disability index (NDI)

2.9.2.1

NDI will be used to assess functional limitations associated with neck pain (29, 30). The questionnaire consists of 10 items addressing pain intensity, personal care, lifting, reading, headache, concentration, work ability, sleep quality, driving, and recreational activities. Each item is scored on a 6-point scale from 0 to 5, where 0 indicates no limitation and 5 indicates complete disability (31). The total scores range from 0 to 50, with higher scores indicating greater functional impairment (32). The NDI demonstrates good reliability and validity, making it an important tool for cervical spine disability measurement (33).

##### 12-item short form survey questionnaire (SF-12)

2.9.2.2

Health-related quality of life will be assessed using the SF-12, which comprises 12 items yielding two summary scores: the Physical Component Summary (PCS) and Mental Component Summary (MCS) (34, 35). Each item is scored on a 5-point scale, and scores for physical and mental health are calculated on a 0–100 scale using the standard American scoring method, with higher scores indicating better self-perceived quality of life (36).

##### Hospital anxiety and depression scale (HADS)

2.9.2.3

HADS was utilized to evaluate NCNP-induced anxiety and depression using 14 items, with 7 assessing anxiety and 7 assessing depression. Each item is scored on a 0–3 scale based on symptom frequency over the past month, with higher scores indicating greater severity of anxiety or depression (37).

##### Pittsburgh sleep quality Index (PSQI)

2.9.2.4

The PSQI is a widely employed self-report instrument for sleep quality assessment. PSQI comprises 18 items across seven components: subjective sleep quality, sleep latency, sleep duration, sleep efficiency, sleep disturbances, use of sleep medication, and daytime dysfunction (38). Each item is scored from 0 to 3, and the global PSQI score ranging from 0 to 21, with higher scores indicating poorer sleep quality. Scores of 0–5 indicate good sleep quality, 6–10 fair quality, 11–15 poor quality, and 16–21 very poor quality.

##### Work productivity and activity impairment questionnaire-specific health problem (WPAI-SHP)

2.9.2.5

WPAI-SHP will be used to investigate absenteeism, work attendance, productivity loss, and daily activity impairment due to illness in the seven days prior to the interview. It can be divided into four scores: absenteeism due to illness, work loss due to illness (when attending work), overall work loss, and activity impairment. All scores are multiplied by 100 and expressed as a percentage, with higher values indicating greater impairment and lower work productivity (39, 40).

##### Cervical range of motion (CROM)

2.9.2.6

Cervical flexion and extension dysfunction is the most common clinical manifestation of nonspecific chronic neck pain. This study will take the cervical range of motion as one of the secondary evaluation indicators. CROM data will include maximum flexion angle and maximum extension angle of cervical. These measurements will be obtained using an advanced infrared high-speed motion capture system (Vicon Motion System, Oxford Metrics, UK), which provides high-precision, instrumented assessment of cervical mobility. Because the operation and maintenance of this technology is costly, it is not feasible to apply it to all participants in the present trial. CROM data will be obtained in approximately 25% of participants in each study group at week 0 and week 8.

### Safety assessment

2.10

Before each treatment session, two research evaluators will document any discomfort reported by participants during or after the previous session and record it as an adverse event (AE), including increased pain, muscle soreness, or exacerbated fatigue. Changes in medication use or additional interventions will also be documented in the case report form (CRF). Serious AEs (requiring hospitalization, being life-threatening, or resulting in death) will lead to trial termination and immediate reporting to the ethics committee. Adverse events will be graded according to a predefined severity scale (Grade 1–5), adapted from Common Terminology Criteria for Adverse Events (CTCAE) version 5.0. Grade 1 events will be monitored without intervention. Grade 2 events will lead to temporary suspension of treatment and symptomatic management. Grade 3 or above will result in immediate discontinuation and reporting to the ethics committee within 24 h. An independent Data Safety Monitoring Board (DSMB) comprising a clinician, a biostatistician, and an ethics expert will regularly review safety data and may recommend early termination.

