### Withdrawal, dropout and removal criteria

2.5

Participants may withdraw from the trial at any time or be discontinued under the following circumstances, as determined by the clinical Data Monitoring Committee (DMC):
Clinically significant exacerbation of NCNP symptoms that severely impairs daily functioning or safety.Unanticipated serious adverse events or complications occur during the trial period, including trauma, allergic reactions, or worsening pain.Occurrence of other serious illness precluding continued participation, such as stroke, hospitalization, surgical interventions, or emergency care.Unblinding for emergencies.Withdrawal deemed necessary at the discretion of the researchers.Participants request to withdraw from the study due to a loss of interest, scheduling conflicts or other personal reasons.We will strive to contact participants who withdraw for any reason to acquire follow-up data and ensure their safety post-trial.

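### Section 2.10 has serious adverse events end the trial without condition, while Section 2.5 treats them as grounds for discontinuing one participant

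*Protocol article*

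**What the plan says.** Section 2.10 (Safety assessment) sets the consequence of a serious adverse event: "Serious AEs (requiring hospitalization, being life-threatening, or resulting in death) will lead to trial termination and immediate reporting to the ethics committee". It then describes steps by severity grade. Grade 1 events are only monitored. For the next level, "Grade 2 events will lead to temporary suspension of treatment and symptomatic management". Above that, "Grade 3 or above will result in immediate discontinuation and reporting to the ethics committee within 24 h". The section closes with an independent DSMB, which "will regularly review safety data and may recommend early termination".

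Section 2.5 (Withdrawal, dropout and removal criteria) deals with individuals. Participants may withdraw or "be discontinued under the following circumstances, as determined by the clinical Data Monitoring Committee (DMC"). Two of the listed grounds matter here: "Unanticipated serious adverse events or complications occur during the trial period, including trauma, allergic reactions, or worsening pain", and, as a separate item, "Occurrence of other serious illness precluding continued participation, such as stroke, hospitalization, surgical interventions, or emergency care". The section ends with a commitment to follow-up: "We will strive to contact participants who withdraw for any reason to acquire follow-up data and ensure their safety post-trial".

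**The concern.** A serious adverse event falls under two rules that act at different levels. Under Section 2.10 the trial ends. Under Section 2.5 a committee decides whether one participant is discontinued, and the team goes on trying to collect that participant's data. Staff who meet the first serious event have to choose between them. If they follow Section 2.10 as written, the trial closes on one event, whether or not it was related to treatment and without review. If they follow Section 2.5 alone, they depart from a written safety rule.

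What would be lost depends on timing. A stop before the last participant reaches week 8 leaves the primary VAS comparison incomplete. A later stop leaves the week-20 and week-32 assessments incomplete, and the Discussion counts the 32-week assessment among the strengths of the design.

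**Working it through.** The check is mainly a comparison of text, since the article gives no figure to reproduce.

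| Rule | Event | Action | Level | Who decides |
|---|---|---|---|---|
| 2.10, serious-event sentence | Serious AE | Termination, report to ethics committee | Trial, as worded | Nobody; automatic |
| 2.5, serious-AE item | Unanticipated serious AE or complication | May be discontinued; follow-up still sought | Participant | DMC |
| 2.10, Grade 2 | Grade 2 AE | Treatment suspended temporarily | Participant | Not stated |
| 2.10, Grade 3 or above | Grade 3 to 5 AE | Discontinuation, report within 24 h | Not named | Not stated |
| 2.10, last sentence | Accumulating safety data | May recommend early termination | Trial | DSMB |

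1. **Is the serious-event sentence conditional?** No. It says these events will lead to termination. It sets no count, no relatedness test and no review step. The article nowhere defines trial termination in a narrower sense.

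2. **Could the term mean the end of one person's participation?** Section 2.5 speaks of participants withdrawing or being discontinued. Within Section 2.10, the other use of termination is for the DSMB's recommendation, which concerns the whole trial. The vocabulary therefore points to the trial level, even if the intention did not.

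3. **Does Section 2.5 cover the same event?** Yes, for unanticipated serious adverse events. A DMC decision about one participant, with continued data collection, has little purpose if the trial has already ended because of that event. This is the firm conflict.

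4. **Grade 3 or above.** This sentence comes four sentences after the serious-event sentence and does not say what is discontinued. The sequence of monitoring, suspending treatment and discontinuing suggests the participant's treatment, but that is an inference. It supports the point without establishing a second contradiction.

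5. **DSMB.** A discretionary recommendation can coexist with an automatic trigger. The fit is poor, but the two are not incompatible.

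**Size.** Read literally, the threshold is one event in any of the 110 participants. How often that would be reached needs a per-participant risk p of a qualifying serious event, which the article does not give. For assumed values, with independent participants and all 110 observed, P(at least one) = 1 − (1 − p)^110:

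- p = 0.2%: 1 − 0.998^110 = 0.20
- p = 0.5%: 1 − 0.995^110 = 0.42
- p = 1%: 1 − 0.99^110 = 0.67
- p = 2%: 1 − 0.98^110 = 0.89
- p = 3%: 1 − 0.97^110 = 0.96

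The result runs from 0.20 to 0.96 according to an input that has to be guessed. It illustrates how sensitive a one-event rule is and is not an estimate for this trial.

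**The case against.** The strongest reply is that this is a slip of wording. Section 2.10 mostly describes what to do for each event, Section 2.5 discontinues individuals, and stopping the whole trial is otherwise left to DSMB advice. A sensible reader would take the sentence to mean the end of that participant's involvement. As a guess at intent this is probably right. It does not cure the text, because a safety rule is carried out as written and this one names the trial.

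A second reply is that the rules could formally coexist. Section 2.5 is permissive, and it covers complications and other events beyond serious ones. Severity grade and seriousness are also different scales, so a non-serious Grade 3 event could discontinue one person while a serious event triggers a stricter rule. This holds for the Grade 3 and DSMB sentences, which is why they count here only as poor fit. It does not remove the overlap with the serious-adverse-event item in Section 2.5.

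A reader might also infer that any hospital admission would close the trial. The article does not support that. Section 2.10 speaks of serious adverse events that require hospitalization, and Section 2.5 places hospitalization under other serious illness, apart from its serious-event item. The text does not settle whether an unrelated admission would count under Section 2.10.

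**Conclusion.** The point holds. The serious-event sentence in Section 2.10 is an unconditional trial-level rule, at odds with the participant-level, DMC-determined handling of serious adverse events in Section 2.5. It also sits awkwardly with the graded steps and the DSMB's role. The conclusion rests on the plain wording and on the absence of any other definition of trial termination in the article.

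The consequence, if the rule is followed literally, is closure on a single event, with the primary or later outcomes possibly incomplete. A reader might infer from this that early closure is likely. The documents give no basis for that: there is no serious-event rate, and under the assumed risks the probability is below one half at 0.2% and 0.5%. Nor does the article support calling the Grade 3 sentence a direct contradiction, since its object is not named. The sentence should be corrected because it is an operative safety instruction and the correction is cheap.

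**What to change.** Amend Sections 2.10 and 2.5 as follows.

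1. Reword the consequence of a serious adverse event to: *will lead to immediate discontinuation of that participant's study treatment and reporting to the ethics committee within 24 h, with outcome follow-up continued where possible*. The 24 h limit is the one already set for Grade 3 or above.
2. Name the same object in the Grade 3 sentence: discontinuation of that participant's study treatment. A serious event of Grade 3 or above then has one rule.
3. State that the DMC's determination under Section 2.5 concerns removal from the trial. Stopping treatment is then automatic, and ending participation is a committee decision.
4. State that stopping the whole trial follows DSMB review and recommendation, and that the DSMB is notified promptly of each serious adverse event.

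The cost is a short protocol amendment and notification of the ethics committee, with no added visits, procedures or participants. The real downside is that an automatic trial stop is replaced by a committee judgement. Prompt notification of the DSMB and the immediate stop of that participant's treatment limit this but do not remove it.
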